All women attending MSHC with vaginal symptoms are assessed for BV using the Nugent method by clinicians as part of their standard care. MSHC has an electronic alert that will trigger whenever clinicians enter the diagnosis of BV into the computerised record, to remind them to offer enrolment in the study to eligible women.  If a woman is interested in participating in the trial, informed consent will be sought by the designated research nurse, who will have been trained in this procedure.

Enrolled women will be randomised to one of the three arms of the study in equal proportions (one third in each arm) using a computer-generated randomisation sequence (see below). A computerised script will be sent to the on-site pharmacy where the treatment kit will be collected by the participant. The contents of the kit will be packaged so as to preserve blinding of clinic staff. Clear instructions on the administration of the oral and vaginal preparations and durations of therapy for each individual will be inside each kit. The participant will collect this kit from pharmacy staff at the end of the visit just prior to departure. Importantly, participants, clinicians and pharmacy staff will not be aware to which arm the participant has been allocated at enrolment. Participants will be reviewed and examined 7-14 days following completion of therapy. It is possible that women may inform a practitioner that they had used a vaginal ovule or cream, potentially identifying the clindamycin arm only but not differentiating between the probiotic and placebo. Due to this small risk of unblinding, assessment of the major trial outcome of BV will only be made using a laboratory diagnosis, as outlined below, not a clinical diagnosis. Laboratory staff, who do not have access to the clinical history, will score vaginal flora (the outcome measure for the study), therefore maintaining blinding. 

Visit procedures
Visit one (at enrolment);

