Women will receive a card and refrigerator magnet with the free call study telephone number, which will be staffed by the study nurse and research investigators. Participants will be encouraged to call the number if they have symptoms of BV during the study or concerns regarding treatment or possible side effects. A sample kit will be supplied to women so that if they are unable to attend MSHC they will be able to self-collect samples for interval symptoms after discussion with the research nurse. Women will be asked in the initial consenting process to allow any results from outside clinics for investigation of BV symptoms to be made available for the study. 

These procedures are similar to those we have previously used in the study of BV recurrence (18,36) and the trial of probiotics for vaginal candidiasis (38).  Only 3/130 and 3/287 women attended outside clinics in these studies as a result of providing easy and rapid review if a woman developed interval symptoms.

Stored samples
With participant consent, vaginal swabs will be stored at -80oC for future examination for potential pathogens. DNA will be extracted using the Magnapure system: MagnaPure LC (Roche Molecular System, Alameda, CA, USA) in accordance with manufacturer's protocol, followed by detection of potential pathogens using molecular amplification technology. 

Study Outcome Measures
Primary outcome measure
Recurrence of BV within 6 months will be defined as a Nugent score of 7-10. We have chosen 6 months rather than 12 months, based on our experience of relapse rates in our previous studies of BV (Figure1). Relapse of BV plateaus by 6 months. Additionally, compliance with follow up will be higher with a 6 month compared to 12 month follow up. 

Secondary outcome measures
1.	Recurrence of abnormal flora within 6 months will be defined by a Nugent score 4-10. 
2.	Behavioural practices and other factors (eg contraceptive use, past history of BV, smoking)  associated with BV recurrence.

Validation of primary outcome
All slides will be stored and re-scored by two independent experienced microbiologists blinded to the intervention group of the participant.  If slides vary in their Nugent score groupings (0-3, 4-6 and 7-10), our experienced laboratory staff will reach consensus using methods from our previous studies of BV recurrence (18, 36). 

Sample size calculation

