The Melbourne Sexual Health Centre (MSHC) is the largest sexual health service in Victoria, and diagnoses 450 cases of symptomatic BV annually.  We estimate a BV recurrence of 50% in study arm 3 (placebo).  A sample size of 123 will be required in each group to detect a 20% difference in recurrence rates (recurrence rate of 30%) between study arm 1 or study arm 2 and study arm 3 with a power of 90% and an alpha of 0.05. Assuming a loss to follow up rate of 20%, 150 women will be recruited in each group. This would involve recruiting 50% of eligible women at MSHC which is consistent with previous studies given a research nurse will be on site to assist.

Evidence of past successful recruitment
Our team has previously successfully recruited women into similar trials.  In a cohort study of BV, we recruited 157 women from MSHC with BV in 12 months despite more restrictive inclusion criteria and no research nurse available to assist with recruitment (18, 36).  Investigators have conducted a 2 year treatment trial of BV (n=130), in which women were followed at regular intervals over 12 months using self-collected sampling in the same manner proposed for this trial. Loss to follow up over 12 months was less than 20% (18, 36). 

Data analysis
Data will be cleaned and entered into an Access database.  Analyses will be intention-to-treat.  Kaplan Meier methods will be used to generate survival curves for time until recurrence of BV and abnormal flora.  Recurrence rates and their 95%CI will be calculated.  Behavioural factors associated with recurrence of BV and abnormal flora will be investigated using a discrete time version of the proportional hazards regression model as proposed by Carlin and colleagues (38). Rate ratios and robust standard errors will be calculated using this methodology.
Randomisation
Sequence generation
Women who provide written informed consent will be randomly assigned using a computer-generated sequence to one of the three study arms. An independent MSHC researcher, with no other input into this trial, will generate and hold the random number sequence. Randomisation will occur in blocks of 15 to ensure that the allocation of women to the three arms occurs at a similar rate over the recruitment period.

Allocation concealment

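### Recruiting 150 women per group covers an 18% loss, not the stated 20%, if 123 are to remain; the effect on power is under one percentage point

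*Protocol*

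**What the plan says.** All the figures stand in one paragraph of the protocol, under Sample size calculation.

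- Control rate: "We estimate a BV recurrence of 50% in study arm 3 (placebo").
- Required number: "A sample size of 123 will be required in each group to detect a 20% difference in recurrence rates".
- Contrast: the aim is to "detect a 20% difference in recurrence rates (recurrence rate of 30%) between study arm 1 or study arm 2 and study arm 3".
- Error rates: the target power is 90%, at alpha 0.05.
- Loss allowance: "Assuming a loss to follow up rate of 20%, 150 women will be recruited in each group".

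The paragraph does not give the number expected to remain after loss, the formula used, or whether alpha is one-sided or two-sided. Elsewhere, Procedures sets equal allocation to the three arms, and the primary outcome is recurrence within 6 months: "Recurrence of BV within 6 months will be defined as a Nugent score of 7-10". Under Evidence of past successful recruitment, the protocol reports that loss in the investigators' earlier 12-month study was below 20%.

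**The concern.** The 150 is presented as the number that absorbs a 20% loss and still leaves the required 123. It does not. Required number, loss rate and recruitment target are linked by a single division, and the three stated values do not satisfy it.

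The stated power rests on that link. The protocol also leans on the calculation later: the section on potential sources of bias cites an adequate sample size as the protection against type I and type II error. If the gap were large, the trial would be less able to detect its target difference than it reports. The size of the gap therefore decides how much the point matters.

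**Working it through.** **Inputs** (Protocol, Sample size calculation, unless noted): p₁ = 0.50 in the placebo arm; p₂ = 0.30 in either active arm; alpha 0.05; power 90%; required n = 123 per group; loss 20%; recruited 150 per group; equal allocation (Procedures). *Assumed, because not stated:* a two-sided test without continuity correction.

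**Step 1. Reproduce the 123.** The mean rate is (0.50 + 0.30)/2 = 0.40, so 2 × 0.40 × 0.60 = 0.48. The sum of the two variances is 0.25 + 0.21 = 0.46.

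- Pooled: n = [1.960·√0.48 + 1.2816·√0.46]² / 0.20² = 124.0, so 124.
- Unpooled: n = 0.46 × (1.960 + 1.2816)² / 0.20² = 120.8, so 121.
- Arcsine: 125.

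The stated 123 lies inside the range 121 to 125, so it is reproduced. A one-sided test would need only 101, which supports the two-sided assumption.

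**Step 2. Check the loss allowance.**

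- Remaining after 20% loss: 150 × (1 − 0.20) = 120, which is 123 − 120 = 3 short per group (2.4%).
- Needed to keep 123 after 20% loss: 123 / (1 − 0.20) = 153.75, so 154 per group, or 3 × 154 = 462 in total against 3 × 150 = 450.
- Loss that 150 can absorb: 1 − 123/150 = 0.18, that is 18%; and 150 × 0.82 = 123.

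Multiplying by 1.20 in place of dividing by 0.80 gives 123 × 1.20 = 147.6, close to 150. This may be where the figure came from, but the protocol does not say.

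**Step 3. Power at 120 and at 123 per group.**

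- Pooled: z = (0.20 − 1.960·√(0.48/n)) / √(0.46/n). At n = 120, z = (0.20 − 0.1240)/0.0619 = 1.23, power 89.0%.
- Unpooled: z = 0.20/√(0.46/n) − 1.960. At n = 120, z = 3.23 − 1.96 = 1.27, power 89.8%.
- Exact: enumeration of the uncorrected chi-square test over all outcomes.

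| Method | Power at 120 | Power at 123 | Difference (points) |
|---|---|---|---|
| Pooled | 89.0% | 89.8% | 0.7 (from unrounded values) |
| Exact enumeration | 89.4% | 89.6% | 0.2 |
| Unpooled | 89.8% | 90.5% | 0.7 |

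The three missing women cost 0.2 to 0.7 of a point. Changing the formula at a fixed n of 120 moves the answer by 89.8 − 89.0 = 0.8 of a point.

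**The case against.** The strongest reply is that nothing of substance follows.

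- The 90% is a round design target, and 89% to 90% meets it for practical purposes. The shortfall is no larger than the spread between standard formulas.
- Counting 120 treats every lost woman as giving no information. The Data analysis section plans intention-to-treat with Kaplan-Meier methods. Samples are due at 4, 8 and 12 weeks and 6 months, and a woman who misses one interval is still contacted at the next. Women lost late therefore contribute events or censored time.
- The earlier loss was below 20% over 12 months, and the follow-up here is half as long.
- A total of 450 is exactly 30 blocks of 15 (450/15 = 30), whereas 462 is not a multiple of 15. Rounding to 150 per group is a plausible practical choice.

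All of this bears on consequence, and there it stands. None of it makes the sentence correct. The calculation is a comparison of two proportions that itself treats lost women as needing replacement, and on those terms 150 does not cover 20%. Earlier loss below 20% makes 18% plausible, but the protocol does not state 18%.

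A reader might go further and infer that the trial fails to deliver its stated power. The figures above do not support that. Nor does it help to say that 123 is one short of the pooled answer of 124: the protocol names no formula, and 123 exceeds the unpooled answer of 121. A continuity-corrected test would give a lower power of 86.3% at 120. However, the protocol specifies no such test, 123 was not derived that way (the corrected requirement is 134), and the same correction already gives about 87% at 123. That drop comes from the choice of test, not from the loss allowance.

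**Conclusion.** The loss allowance is wrong as written: 150 per group less 20% is 120, not 123, and 150 covers 18%. No other part of the protocol repairs it. The arithmetic needs no assumption beyond the protocol's own three numbers.

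The consequence is minor. With 120 evaluable per group, power is about 89% to 90%, and the shortfall itself costs less than one percentage point. This rests on 50% against 30% recurrence, a two-sided alpha of 0.05 and no continuity correction; neither sidedness nor formula is stated. It also rests on lost women contributing nothing, which is pessimistic under the planned analysis. The trial is not materially underpowered, and the point should be treated as a correction to a stated figure.

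**What to change.** Replace the loss sentence under Sample size calculation with one of these:

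1. *150 per group with 20% loss to follow-up gives 120 evaluable women per group and about 89% power (two-sided alpha 0.05)*; or
2. *150 per group allows for 18% loss to follow-up while keeping 123 evaluable women per group.*

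The first keeps the 20% assumption and lowers the reported power slightly. The second keeps the 123 and asks the investigators to stand behind 18%. Whichever is chosen, name the test and its sidedness so that the figure can be reproduced. The cost is one sentence; recruitment, randomisation and analysis are unchanged.

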All treatments for this trial will be identified by a unique trial number, which will tally with the randomisation schedule. Once a woman is enrolled in the study, the RA will telephone the holder of the randomisation schedule to obtain her group allocation. The sequence will be concealed until data analysis is complete.

Blinding
Participants, investigators, research staff, treating clinicians and those assessing the microbiological specimens will all be blinded as to which arm of the trial each participant is allocated. The success of blinding will be tested in the participants with a survey question.

Time Line

Time	Activity	
July-October 2007	Advertise and employ research assistant.
Educate MSHC staff about the trial.
Insert prompt on MSHC computer system
Generation of randomisation schedule
Obtain all interventions and placebos – label with unique study numbers
Assemble study kits	
November 2007 to 2009	Recruitment through MSHC 	
October to February 2010	Data entry
Data analysis
Report writing	

Potential sources of bias and how these will be handled
This trial has been rigorously designed to minimise bias. Potential sources of bias and methods to minimise them are:
·	Selection bias: use of a computer prompt, training of MSHC doctors, and availability of a research nurse to undertake all recruitment, will ensure that all women with a diagnosis of clinical BV will be offered participation in the trial; 
·	Allocation concealment will be maintained by use of a staff member with no other involvement in the trial who will generate and hold the randomisation schedule;
·	Demographic and epidemiological data for all clinic attendees is collected routinely. De-identified epidemiological data of women who decline to take part in the trial will be compared with participants to ensure that the trial participants are representative of the entire eligible population;
·	Treatment bias will be minimised through blinding of treating clinicians and pharmacists to which invention participants have been allocated;
·	Ascertainment bias: the use of a laboratory defined outcome measure, whereby the laboratory staff have no access to the clinical details or intervention group of participants; 
·	Attrition bias: scrupulous follow-up of participants and intention to treat analysis will guard against baseline imbalance in interventions groups;
·	We have calculated an adequate sample size to avoid type I and II errors.

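### The protocol has the RA obtain each woman's group allocation by telephone, which contradicts its own statements that research staff are blinded and the sequence is concealed

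*Protocol*

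**What the plan says.** Four parts of the Protocol bear on this point.

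- **Allocation concealment.** Kits are numbered: "All treatments for this trial will be identified by a unique trial number, which will tally with the randomisation schedule". The section then says "Once a woman is enrolled in the study, the RA will telephone the holder of the randomisation schedule to obtain her group allocation" and closes with "The sequence will be concealed until data analysis is complete".
- **Blinding.** On knowledge of the arm, this section says "Participants, investigators, research staff, treating clinicians and those assessing the microbiological specimens will all be blinded".
- **Sequence generation.** An independent researcher at the centre generates and holds the list. "Randomisation will occur in blocks of 15" gives the only block size; neither varying sizes nor stratification is mentioned.
- **Procedures.** Allocation is in equal thirds. A computerised script goes to the on-site pharmacy, where the woman collects a packaged kit. "Importantly, participants, clinicians and pharmacy staff will not be aware to which arm the participant has been allocated at enrolment". The RA is not in that list.

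**The concern.** The RA belongs to the research staff: the Time Line has the trial hire a research assistant. A call that returns the group gives that person the arm of each woman as she is enrolled, and discloses the sequence one entry at a time. The independence of the schedule holder offers no protection if the holder reads out arms.

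Two things would be at stake. First, a trial described as double-blind would have an unblinded staff member throughout. Second, in blocks of known size, someone who knows the earlier allocations can count down what remains. Selective enrolment, or follow-up effort that differs by arm, would act before any slide reaches the laboratory, and no analysis could restore blinding or concealment afterwards.

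**Working it through.** **Setting the statements side by side**

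1. The RA obtains the group by telephone (Allocation concealment).
2. The sequence is concealed until analysis is complete (same section, next sentence).
3. Research staff are blinded to arm (Blinding).

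Statement 1, read as written, is incompatible with 3 for the RA, and with 2 because the list is disclosed entry by entry. The literal procedure also leaves a gap. If the call returns a group, someone must turn it into a numbered kit, but the pharmacy is blind and nobody else is named for that step.

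**Predictability if arms are disclosed**

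The protocol gives no figure of its own here, so there is none to reproduce. The inputs are:

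- 150 women per group in three groups (Sample size calculation): 3 × 150 = 450.
- Block size 15 (Sequence generation): 450 / 15 = 30 blocks.
- Equal allocation (Procedures): 5 / 5 / 5 in each block.
- Assumption: the observer knows the block size and every earlier allocation in the block.

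*Next arm certain.* This happens when all remaining places belong to one arm. For a given arm, the expected number of its 5 places that fall after all 10 places of the other arms is 5 / (10 + 1) = 5/11. Over three arms this is 3 × 5/11 = 1.364 per block. As a share, 1.364 / 15 = 9.1%. Over the trial, 1.364 × 30 = 40.9, or about 41 of 450. The 15th place of each block is always certain.

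*At least one arm ruled out.* The expected number of places after a given arm is used up is 10 / (5 + 1) = 1.667, so three arms give 5. Subtracting the places where two arms are used up (the 1.364 above) leaves 3.636 per block. That is 3.636 / 15 = 24.2%, and 3.636 × 30 = 109 women.

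*Best guess.* The observer names the arm with most places left. The probability of being right at places 1 to 15, by exact enumeration, is 0.333, 0.357, 0.385, 0.394, 0.405, 0.425, 0.436, 0.449, 0.475, 0.491, 0.510, 0.560, 0.597, 0.643 and 1.000. These sum to 7.46 correct per block, and 7.46 / 15 = 49.7%, against 33.3% by chance.

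**If the call returns only a number that does not reveal the arm**

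The call then gives no information on past arms: 33.3% guessed and 0% certain from this source.

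**The case against.** The strongest reply is that a coded number was meant. Treatments carry unique numbers tied to the schedule, and a pharmacy that does not know the arm can dispense only by number. The neighbouring sentences on concealment and blinding fit that reading. It is plausible, and it prevents anyone from saying that staff were in fact unblinded. It does not rescue the wording, because no sentence says that the call returns only a code.

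A reader might also infer that the RA could steer recruitment, reminders and symptom-triggered sampling, so that bias is established. The documents do not support this. A research nurse is to do all recruitment (Potential sources of bias), and the study nurse and investigators staff the telephone line (Interval BV symptoms and unscheduled visits). Nobody is named for reminders, and nothing says whether the RA is the nurse. The call follows enrolment, so only later women in a block could be affected by selection. A computer prompt is meant to ensure that all eligible women are offered the trial. Laboratory staff score slides without the clinical history, and two blinded microbiologists re-score them. These safeguards limit the risk. They do not cover who gets enrolled or how actively a missing swab is pursued.

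A third inference is that knowing cream from ovule would allow the same counting. Procedures already acknowledges that formulation could identify the clindamycin arm; the call does not cause this. It is also slow. Review comes 7–14 days after 7 or 12 days of therapy, roughly day 14 to 26. At half of 450 cases a year (225), a block fills in 15 / 225 × 365 ≈ 24 days. Much of a block would be enrolled before reviews could reveal its formulations.

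Finally, a block size of 15 may look like a fault in itself. It is five times the minimum for three arms, and it becomes a problem only if past arms are known.

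**Conclusion.** The contradiction is real and lies within adjoining sections of the Protocol: followed literally, the stated procedure breaks the stated blinding and concealment.

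The size figures (about 41 of 450 certain, about 109 with an arm ruled out, about 50% guessed against 33%) are conditional. They require that the arm really is disclosed, that the observer keeps track, and that the block size is known. Even then, about 91% of next allocations are not certain, so predictability concerns part of each block and not the whole sequence.

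Bias in the recurrence comparison is possible but not shown. It would need the informed person to influence enrolment or follow-up, or to tell someone who does, and the protocol does not settle that. The finding is a procedure that is wrong as written and must be reconciled, not evidence that the comparison is biased.

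**What to change.** In Allocation concealment, change what the call returns: in place of the group allocation, the RA obtains the next sequential kit (trial) number, which does not reveal the arm. Add one sentence stating that no one with participant contact holds the key linking numbers to arms. This makes the section consistent with Blinding and with a blind pharmacy.

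The cost is one phrase and one sentence, settled before enrolment starts. It uses the kit numbering already planned and needs no extra patients, staff or product.

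Optionally, vary the block size and keep it from recruiting staff. This adds little once the call returns only a number, but it guards against arms becoming known by another route.

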All participants will have a clinical history taken and undergo speculum vaginal examination, including pH estimation (Spezialindikator strips pH 2-9, Merck & Co., NJ, USA).  After explanation of the trial, women will be invited to participate and to provide written informed consent. Participants will then be asked to complete a questionnaire (regarding behavioural practices, risk factors for STIs, symptomatology {rating scale 1-5}, previous BV episodes and prior treatments). The clinicians will complete a pre-formatted data collection sheet on examination findings (e.g. presence of discharge, nature of discharge), genital specimens will be collected for vaginal microscopy, Chlamydia trachomatis PCR, Neisseria gonorrhoeae culture, and Trichomonas vaginalis culture, and a separate vaginal swab will be stored at -70oC for later analysis.  Following randomisation, study medication will be dispensed as outlined.  

Follow up at 4, 8 weeks, 12 weeks and 6 months
Kits containing a questionnaire, vaginal swab, glass slide, instructions for self-collection, and a prepaid envelope, will be used to examine BV recurrence and factors associated with recurrence at 4, 8 weeks, 12 weeks and 6 months following treatment. The first kit for the 4 week follow-up will be given to participants at the enrolment visit, at which point clear verbal and written instructions will be also be provided and participants given the opportunity to clarify any concerns. Kits for follow-up at 8, 12 weeks and 6 months will be posted to participants. At each follow-up point, participants will be asked about sexual and contraceptive practices, genital symptoms, oral and vaginal self-treatments, and clinician-prescribed therapies. They will self-collect a vaginal swab and make a smear on a glass slide, and return the swab, slide and questionnaire in the prepaid envelope (18). Reminders in the form of telephone calls, letters or SMS text-messages will be sent once she has received the kit by post and weekly after the due date for four weeks. If no specimens are received by this time, the woman will be classified as a non-responder for that interval. Non-responders will still be contacted at the subsequent follow-up point(s). 

Interval BV symptoms and unscheduled visits

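### The Time Line ends analysis and reporting in February 2010, but at the protocol's own recruitment rate the last six-month kits fall due in May 2010 and close in June 2010

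*Protocol*

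**What the plan says.** The Time Line has three rows. The middle one gives recruitment as "November 2007 to 2009", with no end month. The last one gives data entry, data analysis and report writing as "October to February 2010", with no year on October. No row covers follow-up after the last enrolment.

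The section Sample size calculation says that the clinic "diagnoses 450 cases of symptomatic BV annually", that "150 women will be recruited in each group", and of the recruitment needed: "This would involve recruiting 50% of eligible women at MSHC".

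Under Study Outcome Measures the primary outcome is recurrence of BV within six months. Under the follow-up heading, the last kit is timed at six months after treatment. Weekly reminders then run for four weeks past the due date before a woman counts as a non-responder for that interval. Under Intervention, the longest vaginal treatment lasts 12 days.

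**The concern.** The recruitment figures fix how long enrolment takes, and the primary outcome fixes how long each woman must then be followed. Added together, they run past the date by which the Time Line has the report written. Someone following the Time Line would have to analyse before the last women reach the endpoint, or stop recruiting before 450. Otherwise the reporting date must slip. The protocol does not say which, and it gives no date on which follow-up is complete and the database can be locked. What is at stake is six-month information on the women enrolled last.

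**Working it through.** **The plan's own figure.** For 50% v 30%, two-sided alpha 0.05 and 90% power, the pooled-variance formula gives n = [1.960 × √(2 × 0.4 × 0.6) + 1.282 × √(0.25 + 0.21)]² / 0.2² = 124 per arm, against 123 stated. The unpooled formula gives 121. The sample size therefore reproduces closely. The target of 150 per arm is taken as stated: 3 × 150 = 450 women.

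**Recruitment time.** 450 cases a year × 0.50 = 225 women a year, or 18.75 a month, or 0.616 a day. This is an upper limit, because it treats every diagnosed case as eligible. 450 / 225 = 2.0 years. From 1 November 2007, enrolment ends about 31 October 2009.

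**End of follow-up for the last woman.**
- 31 October 2009 + 182 days = 1 May 2010, counting six months from enrolment.
- Adding 12 treatment days gives 13 May 2010.
- Adding 28 days of reminders gives 10 June 2010.

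All three dates fall after February 2010.

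**Women without six-month data at 28 February 2010**, with uniform accrual at 225 a year:

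| Counted before 28 Feb 2010 | Latest enrolment | Enrolled by then | Short of 450 | Rate needed for all 450 |
|---|---|---|---|---|
| Six calendar months | 31 Aug 2009 (22 months) | 22 × 18.75 = 412.5 | about 38 (8%) | 245 a year (55% of cases) |
| 12 + 182 days | 18 Aug 2009 (656 days) | 656 × 0.616 = 404 | 46 (10%) | 251 a year (56%) |
| 12 + 182 + 28 days | 21 Jul 2009 (628 days) | 628 × 0.616 = 387 | 63 (14%) | 262 a year (58%) |

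Counting 182 days instead of six calendar months in the first row gives 39 in place of 38.

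**Can a recruitment end date reconcile the figures?** Not at 50% uptake. The last column shows that 55% to 58% of all cases would be needed just for follow-up to finish on the last day of the window, with no time left for analysis or writing.

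**What would be in hand in February 2010.** The last woman's 12-week kit falls due 31 October 2009 + 12 + 84 days = 4 February 2010. All 450 women would therefore have passed the 4-, 8- and 12-week due dates, although reminders for the very last 12-week kits run to 4 March. Essentially only the six-month kit of the late enrollers is outstanding.

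**The case against.** The Time Line is a short planning table that also covers hiring staff and labelling kits. Nothing in the protocol sets a data cut-off or orders analysis on a fixed date regardless of follow-up. The sections on aims, follow-up and outcome all call for six months. The natural result is that the report comes out later. The table is also loose: recruitment has no end month and October has no year. This stands as far as it limits the consequence. It does not remove the conflict, because no end month in 2009 makes the figures agree at 50% uptake.

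Four stronger readings are tempting, and the protocol does not support them.

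- **That about 31% of women would lack the endpoint.** Counting from 1 October 2009 gives 138 of 450. But that row opens with data entry, which can proceed as kits arrive, and it gives no separate start date for analysis. The close of the window is the fair benchmark.
- **That the six-month comparison would be invalid.** The Data analysis section specifies Kaplan-Meier curves for time to recurrence. Late enrollers would contribute their earlier kits and then be administratively censored. The loss is one of precision in the last interval.
- **That the protocol plans to unblind during follow-up.** The section on allocation concealment keeps the sequence hidden until analysis is complete, so if the analysis waits for follow-up, the sequence waits too.
- **That past uptake was 35%, which disproves the 50%.** The protocol reports that "we recruited 157 women from MSHC with BV in 12 months despite more restrictive inclusion criteria and no research nurse available". Dividing 157 by 450 uses this trial's annual case count, not the number eligible for that cohort, which is not given. The tighter criteria and the absence of a nurse also mean that its rate does not carry over to this trial.

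**Conclusion.** The Time Line is inconsistent with the recruitment assumption and the six-month primary outcome. At 225 women a year, follow-up ends between about 1 May and 10 June 2010, two to three and a half months after the window closes. If the analysis kept to the window, about 38 to 63 of 450 women (8% to 14%) would lack six-month data. The spread depends on whether the treatment days and the reminder window are counted.

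This assumes uniform accrual from 1 November 2007, all 450 yearly cases eligible, 50% of them enrolled, and October read as October 2009. Fewer eligible women or lower uptake would push the dates later. Treating the censoring as harmless apart from lost precision assumes that recurrence risk does not drift with calendar time of enrolment.

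It is a scheduling error that should be corrected. It does not touch the sample size, the endpoint or the analysis method.

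**What to change.** Amend the Time Line as follows:

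1. Give the recruitment end date that the assumed rate implies, about October 2009, and state the rate (225 a year at most).
2. Add a row for completion of follow-up, defined as the close of the last woman's six-month kit and its four-week reminder window, about June 2010.
3. Let data entry run alongside follow-up, but place data lock, primary analysis and release of the allocation sequence after that row.
4. State that these dates move later if 50% uptake is not reached.

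This needs no extra participants, visits or procedures. The cost is a later stated completion date: analysis could not start until about June 2010, whereas the present table has the report finished in February 2010.
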